### 8.2.2.2. Analysis Methods

- For rate of successful accurate diagnosis, the analysis will be similar with the primary analysis.
- For continuous secondary endpoints, the linear regression model will be used to calculate the differences between groups and their 95% CIs using study group as covariate.

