### **7.7.2 Analysis on Secondary Effectiveness Endpoints**

A statistical description of rate of successful accurate diagnosis, duration of angiography, duration of fluoroscopy, flat time and VAS score will be provided, and the linear mixed model will be used to calculate the differences between groups and their 95% CIs using group as covariate and study center as random effect.

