## 1. Summary of Key Protocol Information

### 1.1. Changes to the Protocol Defined Statistical Analysis Plan

Any changes from the originally planned statistical analysis specified in the protocol 1.0 dated 27 Feb 2023 are outlined in Table 1.

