| 
 
The success rate and failure rate of diagnosis will be described, and the causes of failure will be summarized (see Section 2.2 Study Endpoints for details). The Clopper-Pearson method will be used to calculate the 95% confidence intervals (CI) for rate of successful diagnosis in both groups, as well as the difference in rates between the two groups and its 95% CI (Miettinen-Nurminen method). Chi-square tests will be used for non-inferiority tests for rates of successful diagnosis in both groups, and Logistic regression will be used to calculate odds ratio (OR) between the two groups and its 95% CI.
 
 | 
 
The Wald method will be used to calculate the 95% confidence intervals (CI) for rate of successful diagnosis in TRA and TFA groups
 
The difference in rates between TRA and TFA groups will be presented with its 95% CI according to Wald method.
 
A Wald Z test will be used for the non-inferiority hypothesis of the primary efficacy endpoint with a non-inferiority margin of -5%.
 
A generalized linear regression with log link function will also be used to calculate risk ratio (RR) between the two groups and its 95% CI.
 
 | 
 
To keep the consistency between 95% confidence interval and non-inferiority test, the method for calculating confidence intervals for success rates and rate differences was changed to Wald method. And the statistical test was updated from Chi-square test to Wald Z test
 
Since this is a prospective randomized controlled study, we used risk ratio(RR) instead of odds ratio(OR) for between-group comparison
 
 |

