## Sample SAS code

### Linear Regression Model method sample code:

```
PROC GLM DATA = adef;
  CLASS TRTPN;
  MODEL AVAL = TRTPN /SOLUTION DDFM = KR;
  LSMEANS TRTPN /DIFF CL ALPHA = 0.05 e;
  ODS OUTPUT LSMEANS = lsmeans DIFFS = Diffs;
RUN;
```

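### The SAP replaces the protocol's centre random-effect model for the secondary endpoints with a group-only model, does not declare the change, and gives sample code that fits neither model

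*Combined protocol and SAP*

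**What the plan says.** Protocol 7.7.2 takes the five secondary endpoints together: "A statistical description of rate of successful accurate diagnosis, duration of angiography, duration of fluoroscopy, flat time and VAS score will be provided". The same sentence goes on to estimate group differences and 95% CIs from a linear mixed model, "using group as covariate and study center as random effect".

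SAP 8.2.2.2 splits them. For the four continuous endpoints (angiography duration, fluoroscopy duration, flat time, VAS), "the linear regression model will be used to calculate the differences between groups and their 95% CIs using study group as covariate". For the binary one, "For rate of successful accurate diagnosis, the analysis will be similar with the primary analysis", and the primary analysis in SAP 8.1.2.2.2 has study group as its only covariate.

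The input variables in SAP 8.2.2.3 are the response and the planned arm, with no site variable. The sample code opens with "PROC GLM DATA = adef" and continues "MODEL AVAL = TRTPN /SOLUTION DDFM = KR". It has no random statement, and it takes its results from an output table called Diffs.

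On departures from the protocol, SAP 1.1 states: "Any changes from the originally planned statistical analysis specified in the protocol 1.0 dated 27 Feb 2023 are outlined in Table 1". Table 1 has one row of content, on the primary endpoint: the CI method, the test, and the switch from odds ratio to risk ratio. Its rationale for the first two begins "To keep the consistency between 95% confidence interval and non-inferiority test". It says nothing about the secondary endpoints or about centre.

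**The concern.** There are two separate matters.

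The first is traceability. A reader who relies on Table 1 would conclude that the secondary analyses are those of the protocol, and they are not. The SAP is dated 24 January 2025, almost two years after the protocol of 27 February 2023. A change of model with no recorded reason is hard to defend once results are known.

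The second is precision. The documents themselves give grounds to expect differences between sites. The protocol's introduction describes a steep learning curve for radial access that affects procedure and fluoroscopy time. Section 10.3 sets only a minimum of 50 prior angiograms for operators, so experience above that can vary. Fluoroscopy time is read from each site's machine. If such differences exist, a model without centre leaves them in the residual variance.

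The code adds a practical problem. Kenward-Roger degrees of freedom have no function in a model without random effects, so the code does not match the regression that the text describes.

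**Working it through.** **1. The plan's own figures.** The documents give no SD, ICC or target precision for any secondary endpoint, so there is no secondary figure to reproduce. The one computed design figure is the primary sample size of 429 per group. Exact binomial enumeration with a pooled Z test and continuity correction (97% vs 98%, margin -5%, one-sided 0.025) first reaches 90% power at 386 per group, and 386/0.9 = 428.9, which rounds up to 429. That figure does not depend on the secondary model. It supplies the evaluable total used below: 2 × 386 = 772.

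**2. The two models side by side.**

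| | Protocol 7.7.2 | SAP 8.2.2.2-8.2.2.3 |
|---|---|---|
| Continuous endpoints | Linear mixed model | Linear regression |
| Fixed effect | Group | Group |
| Centre | Random effect | Absent |
| Accurate-diagnosis rate | In the same sentence as the others | As the primary analysis, no centre |
| Listed in Table 1 | n/a | No |

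**3. Effect on CI width.** Let ICC be the between-centre share of total variance σ². The group-only model has residual variance of about σ². A model that absorbs centre has about σ²(1 - ICC). With arms roughly balanced within centres, the ratio of CI widths is about

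1/√(1 - ICC).

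The ICC is an assumption throughout. The closed form was checked by simulation with a REML random-intercept fit: 13 centres, 772 patients, 1,000 runs per setting, equal and unequal centre sizes, with and without balancing of arms within centre. Each entry is the mean ratio of the group-only to the mixed-model standard error, and ranges run across equal and unequal centre sizes.

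| Assumed ICC | Closed form | Simulated, arms not balanced within centre | Simulated, arms balanced within centre |
|---|---|---|---|
| 0 | 1.000 | 1.0004-1.0005 | 1.0009-1.0012 |
| 0.01 | 1/√0.99 = 1.005 | 1.0025-1.0027 | 1.0045-1.0048 |
| 0.05 | 1/√0.95 = 1.026 | 1.0173-1.0183 | 1.0220-1.0236 |
| 0.10 | 1/√0.90 = 1.054 | 1.0400-1.0432 | 1.0469-1.0500 |
| 0.20 | 1/√0.80 = 1.118 | 1.0882-1.1027 | 1.0983-1.1087 |

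At ICC 0.01 without balancing within centre, the group-only interval was wider in 70-71% of runs and narrower in 7-11%.

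**4. Validity.** Without balancing within centre, which is the closest setting to the randomisation described in protocol 6.3, coverage of the nominal 95% group-only interval was 0.946 to 0.959 across all ICC values. Omitting centre costs precision there, not coverage.

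**5. The code.** The documents cannot settle SAS syntax, and the code was not run. On general SAS knowledge, DDFM=KR and an output table named Diffs belong to the mixed-model procedure, so PROC GLM would not run this as written. The dataset is also called adef here and adeff in the primary-endpoint code.

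**The case against.** The strongest reply is that little turns on this. No hypothesis test, margin or power is set for the secondary endpoints; the SAP asks only for estimates and 95% CIs. A group-only comparison is valid under the 1:1 randomisation described, and up to ICC 0.10 the loss of precision is about 5% at most. The code is labelled as a sample, and an invalid option would be expected to stop the program, not return a wrong number. All of this stands. It limits how serious the point is, but it does not remove the undeclared departure.

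A reader might infer more than the documents support:

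- **That every secondary CI will be wider.** This holds only on average, and only if between-centre variance is above zero. The documents do not quantify that variance.
- **That the reported standard errors are too large because allocation was balanced by centre.** Neither the synopsis nor protocol 6.3 states stratification by centre.
- **That the centre term was dropped by accident.** The leftover options are compatible with an edited mixed-model template. But the SAP's prose, input list, code label and choice of procedure all describe an ordinary regression, which fits a deliberate simplification at least as well. The documents do not say which it was.

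**Conclusion.** The point holds as an undeclared change of model, together with code that does not match the stated model. Centre is removed for all four continuous secondary endpoints and for the accurate-diagnosis rate, contrary to protocol 7.7.2, and Table 1 is silent although SAP 1.1 says changes are outlined there.

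The expected precision cost is nil at ICC 0, under 1% of CI width at 0.01, 2-3% at 0.05, 4-5% at 0.10 and 9-12% at 0.20. These figures rest on assumed ICCs, about 13 centres and 772 evaluable patients. No bias is shown, and the primary analysis and sample size are not affected. It should be corrected before the secondary analyses are run, but it does not threaten the trial's main conclusion.

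**What to change.** For the continuous endpoints, restore the protocol model in SAP 8.2.2.2 and 8.2.2.3, add SITE to the input variables, and replace the sample code with:

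`PROC MIXED; CLASS TRTPN SITE; MODEL AVAL = TRTPN / SOLUTION DDFM=KR; RANDOM SITE; LSMEANS TRTPN / DIFF CL;`

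Align the dataset name with the primary-endpoint code.

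List in Table 1, with a rationale, any departure that is kept. This includes the method for the accurate-diagnosis rate, where following the primary analysis may be a reasonable choice for a binary outcome but still needs to be declared. If the simpler regression is preferred for the continuous endpoints, declaring it in Table 1 and removing the mixed-model options from the GLM code would cure the inconsistency, at the possible precision cost shown above.

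The cost is SAP wording and a few lines of code. No new data are needed, since each patient's site is known. If the centre variance is estimated as zero, the mixed-model point estimate reduces to the group-only one, so little is risked by restoring it.

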### 8.2.2.3. Model Specifications

#### Statistical Analysis of Continuous Variables

## Endpoints and Parameters

- Endpoints:
  - Duration of angiography
  - Duration of fluoroscopy
  - Flat time
  - VAS score
- Parameters:
  - Mean and 95% CI
  - Difference in means and 95% CI

## Input Variables

- AVAL: Response variable
- TRTPN: Planned arm

## Sample SAS code

### Linear Regression Model method sample code:

```
PROC GLM DATA = adef;
  CLASS TRTPN;
  MODEL AVAL = TRTPN /SOLUTION DDFM = KR;
  LSMEANS TRTPN /DIFF CL ALPHA = 0.05 e;
  ODS OUTPUT LSMEANS = lsmeans DIFFS = Diffs;
RUN;
```

## Results Presentation

- Estimation of mean and 95% CI for both groups:
  - Point estimate: Estimate variable in lsmeans dataset

- Corresponding 95% CI: Lower and Upper variables in lsmeans dataset
- Estimate and 95% CI for difference in means between groups:
  - Point estimate: Estimate variable in Diffs dataset
  - Corresponding 95% CI: Lower and Upper Variables in Diffs Dataset

### 8.3. Subgroup Analysis

If applicable, primary efficacy outcome and secondary efficacy outcomes will be performed in the following subgroups:

- Gender
- Age group
- Height
- BMI
- Diabetes
- Hypertension
- Hyperlipidemia
- History of coronary heart disease
- Smoking History
- History of alcohol use
- Baseline mRS score
- History of Puncture
- Classification of Aortic Arch
- Aortic Arch VariationDegree of Tortuosity of the Aortic Arch and Arch Vessels

## 9. Safety Analyses

### 9.1. Overview of Planned Safety Endpoints Analyses

The safety endpoints analyses will be based on the SS population, unless otherwise specified.

Table 6 provides an overview of the planned safety endpoints analyses.

**Table 6 Overview of Planned Safety Endpoints Analyses**

|                                                           |                          |
|-----------------------------------------------------------|--------------------------|
| QMS Document Name: Statistical Analysis Plan Template(EN) | Page 26 of 38            |
| QMS No (include version ref): STF-015-GL.03               | Document date: 14JUL2022 |
| CONFIDENTIAL                                              |                          |

|                                                                                                                                                      | Data Displays Generated |        |         |
|------------------------------------------------------------------------------------------------------------------------------------------------------|-------------------------|--------|---------|
|                                                                                                                                                      | Table                   | Figure | Listing |
| Adverse Events (AEs)                                                                                                                                 |                         |        |         |
| All Treatment Emergent Adverse Events (TEAEs)                                                                                                        | Y                       |        | Y       |
| Angiography Related TEAEs                                                                                                                            |                         |        |         |
| Moderate and Severe TEAEs                                                                                                                            |                         |        |         |
| Angiography Related Moderate and Severe TEAEs                                                                                                        |                         |        |         |
| Treatment Emergent Serious Adverse Events (TESAEs)                                                                                                   |                         |        |         |
| Angiography Related TESAEs                                                                                                                           |                         |        |         |
| Angiographic Complications During and Within 24 Hours After the Procedure by Type (Access Route Associated Complications/Neurological Complications) |                         |        |         |
| Angiographic Complications During and Within 24 Hours After the Procedure by Severity                                                                |                         |        |         |
| Death                                                                                                                                                |                         |        |         |
| All Death                                                                                                                                            | Y                       |        | Y       |
| Angiography Related Death                                                                                                                            |                         |        |         |

## 9.2. Specifications of Safety Endpoints Analyses

### 9.2.1. Adverse Events

- For adverse events (AE), only treatment emergent adverse events (TEAE) will be summarized in this study, which is defined as: any adverse event that occurs during or within 30 days after the angiography.
- AEs will be coded using MedDRA 24.1 or higher version.
- Frequency tables will be used to summarize TEAEs based on incidences by system organ class (SOC) and preferred term (PT) for each group in descending order in total group, unless otherwise specified. If a subject experienced more than one adverse events in the same SOC or PT, only the one with the highest severity will be counted.

- The investigator will grade the severity of the AE (mild, moderate, severe). AEs with missing severity will not be imputed.
- Angiography related TEAEs including those with a definite, possible, indeterminate, or missing correlation to the angiography.
- The incidences of angiographic complications during and within 24 hours after the procedure will be separately summarized by type (pathway-associated complications/neurological complications) and by severity (major/minor).
- Angiographic complications:
  - Access route associated complications (catheter kink or fracture, artery dissection, artery perforation, artery occlusion, compartment syndrome, arteriovenous fistula, retroperitoneal hematoma, hemorrhage, severe limb ischemia, embolism in any new territory, pseudoaneurysm, subcutaneous hematoma, and arterial spasm, etc.). Any complication which results in permanent sequelae, requires hospitalization, prolongation of existing hospitalization, any surgery or other medical intervention, or leads to death will be considered as a major complication, while all other complications will be considered as minor complications.
  - Neurological complications (cerebral infarction, intracranial hemorrhage, cortical blindness, nerve injury, nervous system infection, contrast encephalopathy, and vasovagal reactions including decreased blood pressure, decreased heart rate, cold sweat, pale, clammy limbs, etc.). Any complication which results in permanent sequelae, requires hospitalization, prolongation of existing hospitalization, any surgery or other medical intervention, or leads to death will be considered as a major complication, while all other complications will be considered as minor complications.

### 9.2.2. Death

The rate of death within 30 days after the procedure and rate of angiography related death within 30 days after the procedure will be summarized, and a list of deaths of the subjects will be provided.

## 10. Exploratory Analyses

### 10.1. Overview of Planned Exploratory Endpoints Analyses

The exploratory endpoints analyses will be based on the TRA group population in the FAS, unless otherwise specified.

Table 7 provides an overview of the planned exploratory endpoints analyses.

|                                                           |                          |
|-----------------------------------------------------------|--------------------------|
| QMS Document Name: Statistical Analysis Plan Template(EN) | Page 28 of 38            |
| QMS No (include version ref): STF-015-GL.03               | Document date: 14JUL2022 |
| CONFIDENTIAL                                              |                          |

